# Antisecretory factor in severe traumatic brain injury (AFISTBI): protocol for an exploratory randomized placebo-controlled trial

**DOI:** 10.1186/s13063-025-08760-7

**Published:** 2025-02-07

## Abstract

**Background:**

Despite recent advances in neuroimaging and neurocritical care, severe traumatic brain injury (TBI) is still a major cause of severe disability and mortality, with increasing incidence worldwide. Antisecretory factor (AF), commercially available as Salovum®, has been shown to lower intracranial pressure (ICP) in experimental models of, e.g., TBI and herpes encephalitis. The aim of this study is to assess the effect of antisecretory factors in adult patients with severe TBI on ICP and inflammatory mediators in extracellular fluid and plasma.

**Methods/design:**

This is a single-center, randomized, placebo-controlled clinical phase 2 trial, investigating the clinical superiority of Salovum® given as a food supplement during 5 days to adults with severe TBI (Glasgow Coma Scale (GCS) < 9), admitted to the neurocritical intensive care unit (NICU) at Skane university hospital, Lund, Sweden. All patients with GCS < 9 and clinical indication for insertion of ICP-monitor and microdialysis catheter will be screened for inclusion and assigned to either the treatment group (*n* = 10) or placebo group (*n* = 10). In both groups, the primary outcome will be ICP (mean values and change from baseline during intervention), registered from high-frequency data monitoring for 5 days. Secondary outcomes will be inflammatory mediators in plasma and intracerebral microdialysis perfusate days 1, 3, and 5 during trial treatment.

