#### Data collection of outcome parameters and predefined covariates

Basic parameters (GCS, GCS-T, age, gender, medical history, diagnosis) are collected from electronic medical charts (Melior) and the monitoring system (IntelliSpace Critical Care and Anesthesia [ICCA] system; Philips) at the NICU. High-frequency data collection of physiological parameters (ICP, CPP, PbtO_2_, pulse, blood pressure, PO_2_, temperature) are sampled with a Moberg® CNS monitor. Brain metabolites (Lactate/pyruvate ratio, glucose, glutamate, glycerol) are analyzed using ISCUS flex (M Dialysis AB). All data from the Moberg CNS monitor and other electronic sources will be transferred to an electronic CRF (Redcap). TIL will be scored every 24 h. TIL will be recorded in a paper CRF and then transferred to the electronic CRF continuously., Plasma samples will be collected before the initial dose of the trial substance, thereafter twice daily for 5 days, and after the last dose of the trial substance. After centrifugation, aliquoted samples will be stored in a − 80 °C freezer. The plasma will be analyzed for markers of brain damage and cytokines/chemokines. Similarly, microdialysis perfusate fluid will be stored in a − 80 °C freezer and analyzed for cytokines/chemokines and markers for brain damage (see Tables 1 and 2). Age, gender, GCS, GCS-T, and trauma mechanism at inclusion, may be used as covariates in exploratory regression analysis. Medical charts are used to track 30-day mortality. Patients or next of kin are followed up by visits and/or telephone interviews at the outpatient clinic in order to assess eGOS > 6 months. All data is stored in a specific password-protected eCRF, only accessible to investigators (Fig. 1).

**Table 1 Tab1:** Primary and secondary outcome measures

Outcome measure	Measure description	Time frame	Objective
ICP mean	Measured by an intracranial pressure sensor	During intervention, 5 days	Primary
ICP area under curve	Measured by an intracranial pressure sensor	During intervention, 5 days	Primary
Inflammatory cytokine secretion	Interleukin-6 (Il-6), interleukin-8 (IL-8), Interferon-gamma inducible protein (IP10) and monocyte chemotactic protein (MCP-1) assessed from microdialysate and plasma by multiplex analysis	During intervention, 5 days	Secondary

**Table 2 Tab2:** Exploratory outcome measures

Outcome measure	Measure description	Time frame
Mortality	Mortality due to TBI	At 30 days and 12 months

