Morbidity	Assessed by Glasgow Outcome Scale Extended (GOSE)	At 6 and 12 months
Intracerebral oxygen partial pressure	Measured by an intracranial oxygen sensor	Change from baseline during intervention
Intracerebral oxygen partial pressure	Measured by an intracranial oxygen sensor	During intervention, 5 days
Treatment intensity level	Treatment intensity level (TIL) scale. Minimum 0 (no intervention to control intracranial pressure (ICP)), maximum 38 points (maximum efforts to control ICP)	Change from baseline during intervention
Treatment intensity level	Treatment intensity level (TIL) scale. Minimum 0 (no intervention to control intracranial pressure (ICP)), maximum 38 points (maximum efforts to control ICP)	During intervention, 5 days
Rate of cerebral metabolism	Lactate/pyruvate ratio assessed by online microdialysis	Change from baseline during intervention
Rate of cerebral metabolism	Lactate/pyruvate ratio assessed by online microdialysis	During intervention, 5 days
Concentration of brain damage markers	Glial fibrillary acidic protein (GFAP), neurofilament light protein (NFL), tubulin associated unit (TAU), and ubiquitin C-terminal hydrolase L1 (UCH-L1)	Change from baseline during intervention
Concentration of brain damage markers	Glial fibrillary acidic protein (GFAP), neurofilament light protein (NFL), tubulin associated unit (TAU), and ubiquitin C-terminal hydrolase L1 (UCH-L1)	During intervention, 5 days
ICP mean	Measured by an intracranial pressure sensor	Change from baseline during intervention
ICP area under curve	Measured by an intracranial pressure sensor	Change from baseline during intervention
Inflammatory cytokine secretion	Interleukin-6 (Il-6), interleukin-8 (IL-8), interferon-gamma inducible protein (IP10) and monocyte chemotactic protein (MCP-1) assessed from microdialysate and plasma by multiplex analysis	Change from baseline during intervention

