#### Inflammatory mediators

Inflammatory cytokines are analyzed from microdialysates and blood using single and multiplex techniques; Mesoscale (Mesoscale Discovery) and O-link (O-link proteomics).

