#### Handling of missing data

With the exception of TIL, the data collected in this trial is limited to what is normally measured and registered during standard care at the NICU. Therefore, the amount of missing data is expected to be low. Data missing at random will be handled using the last observation carried forward (LOCF). Data not missing at random will be analyzed using mean substitution. If microdialysis is not initiated or fails after insertion, the patient will be given the trial substance or placebo as scheduled, but additional patients will be added in order to achieve 20 patients monitored with microdialysis data for a minimum of 3 days.

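### The secondary cytokine outcome is given three unreconciled time frames, and the missing-data rule lets a day-5 dialysate value be an earlier value carried forward or a mean

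*Protocol article*

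**What the plan says.** The protocol article describes the secondary cytokine outcome in several places.

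- **Abstract, Methods/design:** "Secondary outcomes will be inflammatory mediators in plasma and intracerebral microdialysis perfusate days 1, 3, and 5 during trial treatment".
- **Table 1:** the markers are "Interleukin-6 (Il-6), interleukin-8 (IL-8), Interferon-gamma inducible protein (IP10) and monocyte chemotactic protein (MCP-1) assessed from microdialysate and plasma by multiplex analysis", with the five-day intervention as the only time frame. Table 2 lists change from baseline in the same cytokines as a separate, exploratory outcome.
- **Data collection of outcome parameters and predefined covariates:** "Plasma samples will be collected before the initial dose of the trial substance, thereafter twice daily for 5 days, and after the last dose". For dialysate the section covers storage and assay but gives no sampling times.
- **Inflammatory mediators:** "Inflammatory cytokines are analyzed from microdialysates and blood using single and multiplex techniques", naming two assay platforms without listing analytes.
- **Handling of missing data:** if microdialysis is not started or fails, further patients are recruited until there are "20 patients monitored with microdialysis data for a minimum of 3 days". Data missing at random are filled by LOCF, and data not missing at random by mean substitution. No exception is made for cytokines.
- **Statistical analysis:** continuous data go to Mann–Whitney and Wilcoxon tests, and the reader is sent to Additional files 1 and 3 for detail. Those files are not at hand.

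**The concern.** This is the trial's only secondary endpoint, and the article cannot be used to say which measurements make it up. For plasma it could be three days, one figure for the whole window, or every sample drawn.

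The missing-data rule adds a second difficulty. Day 5 is a named outcome day for dialysate, yet a patient with 3 days of microdialysis already counts toward the target. Where day 5 is absent, the stated rules supply a number that was not measured on that day. Cytokines move over the first days after injury, so the substitute can differ systematically from the missing value. If monitoring ends earlier in one arm, part of the arm difference on day 5 would come from the fill-in rule.

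The named tests also need one value per patient. If that value is taken day by day, the number of comparisons grows quickly, and a chance result in one marker, fluid and day could be read as an effect on neuroinflammation, which the Discussion gives as an aim of the study.

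**Working it through.** The article states no alpha level, test count or error rate for the cytokines, so there is no figure to reproduce.

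**1. Time points**

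| Place | Time frame | Values per patient and marker |
|---|---|---|
| Abstract | days 1, 3, 5 | 3 per fluid |
| Table 1 | five-day window | not stated |
| Data collection (plasma) | pre-dose, twice daily, after last dose | 1 + 2 × 5 + 1 = 12 |
| Data collection (dialysate) | none given | not stated |

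Days 1, 3 and 5 lie inside both the window and the plasma schedule. The plasma outcome could still rest on 3 values or on as many as 11 after the first dose (2 × 5 + 1).

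**2. The missing-data rule applied to day 5**

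Let a patient's dialysate values be x1, x3 and x5, with monitoring ending after day 3.

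- LOCF sets x5 = x3. The day-5 error is x3 − x5, and the three-day mean becomes (x1 + 2·x3)/3. If k of the 10 patients in an arm are filled this way, that arm's day-5 mean shifts by (k/10) times their average x3 − x5. Each such patient is one tenth of the arm.
- Mean substitution, in its usual sense, inserts an average taken from other patients. If k of 10 receive the mean of the 10 − k observed values in their arm, the sum of squares is unchanged but the divisor rises from 9 − k to 9. For k = 3, chosen only as an illustration, the variance falls to 6/9 = 0.67 of its observed value. In a rank test the filled values are tied.

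The article gives neither k nor the size of the change over time, so the net bias cannot be calculated.

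**3. Size of the multiplicity, if testing were day by day**

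Inputs: 4 cytokines and 2 fluids (Table 1), 3 days (abstract), 10 against 10 patients (abstract). Assumption: two-sided 0.05 per test, unadjusted. Tests: 4 × 2 × 3 = 24. One summary per cytokine and fluid would give 4 × 2 = 8.

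Under independence, the chance of at least one false difference is 1 − 0.95^m. In the favourable direction only, it is 1 − 0.975^m. The exact Mann–Whitney test at 10 against 10 rejects at U ≤ 23 or U ≥ 77, with size 0.0433 (0.0216 per side). The last row of the table comes from 20,000 simulated null trials per setting, with assumed correlations of 0 to 0.7 between markers, 0 to 0.5 between fluids and 0 to 0.8 between days (no day dimension for the 8 summaries, where the fluid correlation ran from 0 to 0.3).

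| | 24 tests, any | 24 tests, favourable | 8 tests, any | 8 tests, favourable |
|---|---|---|---|---|
| Independent, 0.05 | 70.8% | 45.5% | 33.7% | 18.3% |
| Independent, exact size | 65.4% | 40.8% | 29.8% | 16.1% |
| Simulated, exact test | 41–65% | 21–41% | 22–30% | 11–16% |

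**The case against.** Much can be said for the plan, and several stronger readings fail.

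- **That the sections contradict each other.** Frequent sampling and freezing, with days 1, 3 and 5 chosen for analysis, is a coherent design. The fault is only that no section says so.
- **That day-5 dialysate is missing by design.** Three days is a minimum for counting a patient. Treatment and outcome run for five days, and the article expects little missing data. Day 5 is allowed to be absent, not planned to be.
- **That 24 tests, or far more, are planned.** No section states day-by-day testing, and Table 1's window fits one summary per marker and fluid. A count of 4 × 2 × 12 = 96 would apply the plasma schedule to dialysate and include the pre-dose sample, which cannot show a treatment effect.
- **That a false anti-inflammatory finding is more likely than not.** That claim has a direction. With 24 tests the chance is at most 45.5%, and it passes one half only at 28 independent tests (1 − 0.975^28 = 50.8%).
- **That the lack of a summary measure or multiplicity rule is itself a defect.** An analysis plan commonly holds these, and the article points to files not shown. The trial also calls itself exploratory.

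All five replies stand. They do not answer the missing-data point: the 3-day minimum, LOCF and mean substitution are written in the article, with no exception for a marker whose named outcome days include day 5.

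**Conclusion.** The point holds in a limited form. The time frames of the secondary cytokine outcome need to be reconciled. The stated completeness and imputation rules allow a day-5 dialysate cytokine to be an earlier value relabelled or an average that is not the patient's own. With 10 patients per arm, a few such values matter.

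The false-positive figures are conditional. They assume that each marker, fluid and day is tested separately at two-sided 0.05 without adjustment: up to about 71% for any false difference (about 41–65% under the assumed correlations), and up to about 46% in the favourable direction. They show why one value per patient should be fixed in advance. They do not describe what the sponsor has said it will do. The primary ICP outcome is not affected by this point.

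**What to change.** Before unblinding, make these changes:

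1. State the same cytokine analysis days in the abstract, Table 1 and the data-collection section, for plasma and for dialysate.
2. For each of the four named cytokines in each fluid, compare one value per patient: the mean log concentration over the available on-treatment analysis days. Adjust for the pre-dose plasma value, and for a pre-dose dialysate value only where one exists. This uses a sample already collected and is distinct from the change-from-baseline outcome in Table 2.
3. Exempt missing dialysate cytokines from LOCF and mean substitution.
4. Label per-day results and any wider protein panel as exploratory.

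Multiplicity control over the 8 summaries is optional in an exploratory trial. Without it, the chance of at least one false difference is about 34% if they are independent, so the report should say that the p-values are unadjusted.

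The cost is wording only, with no new samples or assays. One summary can miss a short-lived effect, which per-day plots would still show. Patients with fewer days give a less precise mean, taken from an earlier part of the course. The number of days behind each mean should therefore be shown by arm, and the dialysate comparison repeated on days 1 and 3 alone as a check.

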**Trial registration:**

ClinicalTrials.gov NCT04117672. Registered on September 17, 2017. Protocol version 6 from October 24, 2023.

**Supplementary Information:**

The online version contains supplementary material available at 10.1186/s13063-025-08760-7.

## Introduction

Despite recent advances in neuroimaging and neurocritical care, severe traumatic brain injury (TBI), frequently referred to as a silent epidemic, remains a major cause of severe disability and mortality with increasing incidence worldwide [1–6]. Cerebral edema is an important secondary injury mechanism, which accounts for an essential part of the morbidity and mortality in severe TBI [7]. The complex pathophysiological mechanisms causing the development and brain edema in severe TBI are poorly understood [2, 8–10]. However, the development of edema may cause raised intracranial pressure (ICP) that is considered critical with impact on both perfusion and diffusion in the brain [8, 9], resulting in deleterious effects on brain function [11].

Anti-secretory factor (AF) is an endogenous anti-inflammatory protein [12] that has shown clinical effects on Ménière’s disease and childhood diarrhea [13–15]. The exact mechanisms underlying the effects of AF are yet to be discovered, however, modulation of ion pumps, proteasomes, complement factors, and myeloid cells have been proposed [16]. In experimental models of TBI and herpes encephalitis, AF reduces ICP and improves outcomes [17, 18]. The AF protein is cleaved into several active peptides, one of which has been synthesized within a 16 amino acid peptide (AF-16) that has been used in animal experimental studies [17]. Salovum® (19) is a product based on the egg yolk powder B221® and contains high levels of AF. Salovum® is classified as a food for special medical purposes (FSMP) by the European Food Safety Agency. Salovum® has been given to hundreds of patients in clinical trials without any reports of adverse events [14, 15, 19, 20]. Egg yolk allergy is a contraindication, but no cases of triggered allergy have been reported. Beneficial effects of Salovum® in patients with severe TBI have been reported in small case series [21, 22] and a recently completed randomized trial has studied the effect of Salovum® on 30-day mortality in patients with severe TBI [23]. However, sampling ICP values once per hour is a crude measurement, and none of these studies have recorded ICP using frequency data sampling and analysis of inflammatory mediators. If this trial can demonstrate effect of Salovum® on ICP, a new and safe therapeutic option for ICP management in clinical practice would be available.

## Methods/design

### Trial design

This is a single-center, investigator-sponsored, phase 2, randomized, placebo-controlled, parallel-arm trial to assess the superiority of AF given as Salovum® in patients with severe TBI. The allocation ratio is 1:1. Recruitment commenced in March 2020.

### Trial population and eligibility

A total of 20 patients with severe TBI will be enrolled at a single study site, Skane University Hospital, Lund Sweden. Patients with a Glasgow Coma Scale (GCS) score < 9 and clinical indication for insertion of ICP monitor, intracerebral oxygen pressure monitor (Licox®), and microdialysis catheter will be screened for inclusion.

### Inclusion criteria

The inclusion criteria are as follows: patients with severe TBI, i.e., GCS < 9 at admission to NICU or within 24 h of injury; planned for neurointensive care including ICP-monitoring, microdialysis, and intracerebral oxygen pressure monitoring; aged between 10 and 70 years; pathological findings on initial CT scan.

### Exclusion criteria

The exclusion criteria are as follows: known egg yolk allergy; unilateral or bilateral fixed and dilated pupil(s) after initial surgical intervention; non-fulfillment of inclusion criteria after screening.

### Management of traumatic brain injury

The study site will treat all study patients according to the hospital standard care that may include assisted ventilation, use of invasive ICP monitors, head elevation, hyperventilation, barbiturate coma, drainage of cerebrospinal fluid (CSF), and surgical measures to lower ICP, including decompressive craniectomy.

### Study participants

Study participants will be composed of 20 patients with severe TBI (GCS < 9) who are planned for neurointensive care, including ICP monitoring, microdialysis, and intracerebral oxygen pressure monitoring. When a patient with severe traumatic brain injury is admitted to the neurointensive care unit, the neurosurgeon on call or study investigator will evaluate the patient, provide next of kin with informed consultation, and use the screening protocol for inclusion. For patients < 18 years, signed informed consent by next of kin is required for inclusion.

### Ethics and protocol

Ethical approval has been granted by the Swedish ethical review authority (2019/1). The study will comply with the ethical principles as set down in the Declaration of Helsinki and will be conducted in accordance with good clinical practice as defined by the International Conference on Harmonization (ICH). The trial is registered with ClinicalTrials.gov, NCT04117672; any amendments to the protocol will be published on ClinicalTrials.gov.

### Randomization

Patients in the trial are allocated to treatment with Salovum® or placebo egg yolk powder at a ratio of 1:1. The allocation sequence is generated by the principal investigator. Permuted block randomization, with blocks of 4–6, will be used and was compiled with R. Each patient is assigned a sequentially numbered study binder. The study number written in the binder corresponds to a sealed and opaque box with the same number, containing the study substance, either active (Salovum®) or placebo (normal egg yolk powder). Study substance and placebo appear identical with respect to packaging, color, texture, and smell. Investigators, caregivers, and patients are blinded during the entire trial. If any patient needs unblinding for medical reasons, an emergency unblinding list exists in digital form.

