#### Handling of protocol deviations and protocol violations

We defined 4 types of possible protocol deviations/violations in this trial: faulty enrolment of patients (enrolment of ineligible patients), faulty randomization (if patients are given the wrong randomization number), faulty intervention (if patients are given wrong intervention and/or do not adhere to the protocol), and faulty data collection. The primary investigator is responsible for enrolment and randomization of patients. TIL is noted daily by investigators. Daily visits are made by the investigator and/or research nurse to ensure correct administration of trial substance, sampling of blood/perfusate, and data collection. Any protocol violation/deviation will be disclosed at the end of the trial as described in previous paragraphs.

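### One role generates the allocation sequence and is responsible for enrolment and randomisation, so concealment and blinding are not secured for that role as the article is written

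*Protocol article*

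**What the plan says.** Three statements in the protocol article bear on this.

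- Randomization, on the sequence: "The allocation sequence is generated by the principal investigator". On the method: "Permuted block randomization, with blocks of 4–6, will be used and was compiled with R".
- Handling of protocol deviations and protocol violations, on entry: "The primary investigator is responsible for enrolment and randomization of patients".
- Randomization, on blinding: "Investigators, caregivers, and patients are blinded during the entire trial". No exception is made for whoever produced the list.

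The safeguard described is physical. Binders are numbered in sequence, and "The study number written in the binder corresponds to a sealed and opaque box with the same number, containing the study substance". Active and placebo powder look the same and come in identical bags. For emergencies, "an emergency unblinding list exists in digital form", with no holder named. Under Study participants, "the neurosurgeon on call or study investigator will evaluate the patient" and applies the screening form. On daily scoring of therapy intensity, the section on protocol deviations says: "TIL is noted daily by investigators".

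**The concern.** Numbered opaque boxes conceal the next assignment only from people who do not know which number carries which arm. The author of the sequence can know that for every number. If the same role also decides who enters and when, two protections are in doubt for that role: concealment before entry and blinding afterwards.

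What is at stake is the comparability of two arms of ten. A person who knows the next assignment can include or pass over a candidate accordingly. After entry, the same knowledge can influence ICP-lowering care, which the article leaves to hospital standard care and which acts directly on the primary outcome. To a lesser degree it can influence TIL, an exploratory outcome scored by investigators. No analysis can undo selection at entry.

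**Working it through.** **Roles side by side.** The article gives no figure on this point to reproduce, so the first step is a comparison of statements.

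| Task or status | Who, according to the article |
|---|---|
| Generates the sequence | Principal investigator |
| Responsible for enrolment and randomisation | Primary investigator |
| Screens at admission | On-call neurosurgeon or a study investigator |
| Scores TIL daily | Investigators |
| Holds the digital unblinding list | Not named |
| Blinded throughout | All investigators, caregivers and patients |

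If principal and primary investigator are one role, rows 1, 2 and 6 can all hold only with a safeguard that keeps the author from seeing the list. The article describes none. Block size and packaging do not matter to someone who has the list.

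**Room for selection.** The article gives about 15 severe TBI patients a year, a start in March 2020 and an estimated end on December 30, 2024, which is about 4.8 years.
- 15 × 4.8 = 72 patients for 20 places, and 72 / 20 = 3.6 per place.
- This is an upper bound. Eligibility also requires age 10 to 70, CT pathology and planned multimodal monitoring, and excludes egg yolk allergy and fixed dilated pupils.

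**Size of the possible bias.** Assumptions, none of them from the article: no drug effect; normally distributed mean ICP with equal SD; the enroller gives an active place to the lower-ICP of two candidates; what the enroller sees predicts later ICP perfectly.
- The expected minimum of two standard normal values is −1/√π = −0.564.
- All ten active places steered: shift 0.564, or about 0.56 SD.
- Three of ten active places steered: 0.3 × 0.564 = 0.169, or about 0.17 SD.

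The false-positive rates come from simulating a two-sided exact Mann–Whitney test at 5% with 10 per arm (40,000 runs per scenario):

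| Scenario, no drug effect | Shift (SD) | False positives |
|---|---|---|
| No steering | 0 | about 4% |
| Three active places steered | 0.17 | about 5% |
| All ten active places steered | 0.56 | about 22% |
| All ten active, correlation 0.5 between what is seen and later ICP | 0.28 | about 8% |
| All 20 places steered, arms in opposite directions | 1.13 | about 78% |

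For comparison, the same test has 80% power at a true difference of about 1.4 SD.

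**The case against.** The strongest reply is that knowledge of the list is inferred. The article says who generated the sequence and that it was produced in R. It does not say who kept the list, who matched it to the boxes or who holds the unblinding file. The full protocol, an additional file not shown here, may describe a safeguard. The article also says principal in one place and primary in the other, and the second sentence may assign accountability rather than bedside enrolment. These points stand as limits. They do not remove the conflict, because the article itself assigns the roles and makes an unqualified blinding claim.

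A reader might infer that allocation concealment is defeated for the whole trial. The text does not support that. The on-call neurosurgeon may screen, and for that person, other investigators and caregivers the boxes and identical powders can still work.

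A reader might also infer that a few steered inclusions could produce an entire treatment effect. The calculation does not bear this out: three steered active places barely move the false-positive rate. The larger figures need all places steered and perfect foresight. At 15 patients a year one arrives about every 52 / 15 = 3.5 weeks, so two candidates would rarely be present together and steering would mean skipping patients in turn. ICP monitoring need only be planned at inclusion, so ICP may not yet be known.

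Finally, the primary outcome is recorded by a monitor at high frequency, which limits bias in reading it, and TIL is exploratory and not assigned to the principal investigator in particular. Both points are fair. Influence on the care that drives ICP remains possible.

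**Conclusion.** The point holds in limited form. As the article stands, one role can know every assignment while being responsible for entry, and is also described as blinded. These statements are not reconciled, so concealment and blinding are unsecured for that role and may be intact for everyone else.

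The possible bias runs from negligible (about 0.17 SD, 5% false positives, three active places steered) to serious (about 0.56 SD, 22%, all ten). The second figure is an illustrative upper bound for steering one arm between two candidates, because it assumes perfect prediction. Steering both arms throughout would be worse, but nothing in the article points to it or to any steering at all.

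The conclusion rests on reading principal and primary investigator as one role. If they are two people, the article needs to say so, and the blinding statement still needs an exception for anyone who has seen the list.

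**What to change.** Because recruitment was estimated to end on December 30, 2024, and the article appeared on February 7, 2025, disclosure and correction come first.

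1. State who generated the sequence, who has seen it, and who holds it and the digital unblinding list. If a safeguard kept the author from seeing the list, describe it.
2. Limit the blinding statement to those who are in fact blinded.
3. Transfer the sequence and the unblinding list to a person with no role in enrolment, care or assessment, for example at Forum South, which already monitors the trial.
4. Keep anyone who has seen the list out of further enrolment, TIL scoring and outstanding GOSE assessments. Existing blinded investigators can take these over.
5. If unused numbers remain, have the independent person regenerate them and match the boxes.
6. Report screened versus enrolled patients, so that readers can judge how much selection was possible.

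Items 1, 2 and 6 cost only text and a screening count. Items 3 and 4 reassign existing staff. Item 5 needs an unblinded person to relabel sealed boxes and may break a block part-way, with some risk to balance in 20 patients; it falls away if no numbers are left. No new patients or procedures are needed.
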